#### Baseline variables

##### Quality of health information

Each provider’s most recent health information, which meets the criteria of materials giving information towards a health-related decision, will be rated regarding quality using the *Mapping Health Information Quality* (MAPPinfo) Checklist.

##### Critical health literacy

Critical health literacy will be assessed using the *Critical Health Competence Test* (CHC test) [36]. The test is based on a 4 × 4 facets design. The first facet consists of four different and relevant content areas of healthcare. The second facet is built up with four subareas of competence, representing the underpinning theoretical structure of the critical health literacy construct. These categories are: A. Understanding medical concepts; B. Skills of searching literature; C. Basic statistics; and D. Design of experiments and sampling. Reliability of the test for the Rasch model (analysis of variance (ANOVA)) was 0.91 and for the single scenarios 0.71 (scenario 1); 0.78 (scenario 2); 0.75 (scenario 3) and 0.80 (scenario 4).

The CHC test comprises four different scenarios which allows testing at different time points using different scenarios. The test will be carried out at baseline and as part of the process evaluation after the training programme in the IG and the CG. Critical health literacy will be aggregated at group level using the maximum of individual values from the CHC test.

### Outcomes and data collection

#### Primary outcome

The primary outcome parameter is the quality of health information as measured using the MAPPinfo Checklist. Assessment of the primary outcome requires the providers to deliver one work sample in the form of health information. Other information produced during the study period will not be considered. The work sample has to inform a decision in healthcare (e.g. therapy, diagnostic procedure, screening, prevention or rehabilitation). It addresses patients or medical laypersons and discusses at least two options regarding a specified health problem. Material regarding procedures (e.g. how to perform peritoneal dialysis at home) or the healthcare system, resources giving general advice for health and wellbeing as well as (drug) fact(s) boxes without additional text are not appropriate. Despite these requirements, the providers are free to choose the topic and target group of the information. Therefore, they can further develop already planned information. The providers may use external services (e.g. counselling by experts, graphic design, external performing of pilot tests or external literature searches), but they are responsible for the methods applied and for the content and design of the final information.

The quality of the health information is defined as the extent of adherence to the guideline‘s recommendations. This parameter is operationalised by the MAPPinfo instrument that has recently been developed for this very purpose. MAPPinfo corresponds with the recommendations of the guideline and is the first instrument using exclusively evidence-based quality criteria. By the time it is used in our study, MAPPinfo will have passed all the validation steps. The study protocol for the validation study is in the process of publication. Information on reliability, internal consistency, construct validity, criterion validity and divergent validity will then be available. The instrument comprises 21 to 23 test items (depending on the nature of the addressed decision) in four categories:
Definitions (comprising target group and aim of the health information)Transparency (comprising disclosure of authors, financing, conflicts of interest, level of actuality, sources of information and strategies of information gathering)Content (comprising explanations of the medical problem, available options and uncertainty, and information about prevalence, (test quality (if relevant), benefit and harms) andPresentation (comprising prevalence, test quality (if relevant), benefits, harms, language, patient stories, graphics and gain-loss framing)

The instrument just focusses on criteria accessible through observation of the health information itself and does not consider quality criteria related to development methods or correctness of the contents, which would require further information sources. Adherence to the criteria checked by MAPPinfo is essential but not sufficient to provide material that improves informed decision-making. Non-adherence with one of the criteria may already challenge the entire information process. Therefore, all the criteria should be met. Nevertheless, the instrument provides percentage scores for each category and for each criterion. In this study, scores based on MAPPinfo will be expressed as a percentage of the fully met criteria. Therefore, the items will be coded as fulfilled (100%), partly fulfilled (50%) or not fulfilled (0%). Scores for information quality will be generated (range 0–100%) as an average over all items. MAPPinfo coding works without previous training. The information will be coded by two independent and blinded raters.

#### Secondary outcomes

Due to the pronounced importance of single aspects of the quality concept, it is planned to use a selection of single criteria as secondary outcomes. For this purpose, single criteria are chosen following strong recommendations based either on empiric effects or on ethical considerations:
CONTENT 5/PRESENTATION 2: ‘Information about possible benefits is provided in an appropriate manner’CONTENT 6/PRESENTATION 3: ‘Information about possible harm is provided in an appropriate manner’CONTENT 7/PRESENTATION 4: ‘In the case of diagnostic problems: information about the reliability and safety of the test are provided in an appropriate manner’PRESENTATION 5: ‘The health information uses a neutral wording/language throughout’DEVELOPMENT: ‘The health information target group has been involved in the development process using appropriate methods’

All these secondary outcomes are binary.

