**Fig. 3 Fig3:**
[figure not shown]
Standard Protocol Items: Recommendations for Interventional Trials (SPIRIT) Figure

Completed health information can be sent to the study team at any time. After 10 months, the development process should be concluded and the providers will be asked for the material. A provider who cannot deliver after 10 months can be given a 2-month extension of the deadline. The provider should give a justification for the delay and a reasonable timeline for the following 2 months.

After 12 months (*t*_2_), even unfinished material must be submitted. The information will be rated with regard to the primary outcome. Single criteria (or else the entire information) that do not meet the MAPPinfo requirements, are coded as zero. Providers of both groups (IG and CG) who completed their information will be asked to give further information on the development process (*t*_3_). Interviews will be conducted in the IG to explore barriers and facilitators of implementation (cf. process evaluation). The providers in the CG will be invited to make appointments for the training programme (*t*_3_). After the provided information has been rated, providers may receive individual feedback on their material. This is optional, but this way the feedback would benefit especially the providers in the CG.

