#### Process evaluation

To support future implementation of the *guideline evidence-based health information* and the training programme, a comprehensive analysis of the underlying processes of this complex intervention is indispensable [38]. Barriers and facilitators of implementation should be assessed. Additionally, the high quality of the training programme should be ensured. We will focus on parameters such as recruitment, reasons for participation or non-participation, intervention fidelity, structure and process-related factors, attitudes toward the intervention, response of individuals and organisations, and unintended consequences [38, 39]. Mixed methods will be applied [40] according to the MRC framework for process evaluation of complex interventions [38].

Structured documentation will be used to assess data of recruitment and intervention fidelity (e.g. recruitment process; numbers of institutions invited, responses and participants in each training session; location, time and duration of the training; completeness of modules and online tasks and reasons for deviations; and unexpected difficulties). Feasibility and acceptance of the training programme will be assessed at the end of the training sessions using structured feedback, and all statements will be documented. Critical health literacy will be assessed using the CHC test [36] after the IG and CG have completed the training programme.

To map the development process and the methodological quality of the produced health information, all the providers (IG and CG) will be asked to provide the MAPPinfo self-declaration after completing the health information. The self-declaration comprises free-text questions on the selection of the reported options and outcome measurements, search strategies, methods of data extraction and critical appraisal, reasons for the use of pictures, graphics, fact boxes, value clarification tools, animations and interactive tools. Experts will review the results and, if there are outstanding issues, interviews will be conducted. In addition and to identify influencing factors, the resources and support used in the development process as well as any training attended during the study period will be assessed.

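### The target-group involvement outcome needs information that is requested only from providers who finish their item, so non-finishers would have no value

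*Protocol article*

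**What the plan says.** Protocol article, Secondary outcomes: five single criteria are selected. The last, labelled DEVELOPMENT, is whether "The health information target group has been involved in the development process using appropriate methods". The section adds: "All these secondary outcomes are binary".

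Primary outcome: MAPPinfo has four categories (definitions, transparency, content, presentation), and it "does not consider quality criteria related to development methods or correctness of the contents, which would require further information sources".

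Procedure (text after Fig. 3): an item not ready at 10 months may get a 2-month extension, and at 12 months (t2) unfinished material must also be handed in. After that, at t3, providers of both arms "who completed their information will be asked to give further information on the development process".

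Process evaluation: "all the providers (IG and CG) will be asked to provide the MAPPinfo self-declaration after completing the health information". Experts review the answers and hold interviews where issues remain open.

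Data management, protection and analyses: the binary secondary outcomes are described as relative frequencies by arm and compared with Fisher's exact test.

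**The concern.** Four of the five secondary outcomes can be read off the submitted item, finished or not. DEVELOPMENT cannot: it needs a report from the provider. The article makes that report follow completion of the item. A provider that submits unfinished material at t2 contributes to the primary outcome but, on the stated collection rule, is never asked how its item was developed.

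Completion occurs after randomisation and could be related both to arm and to the outcome. The intervention group begins production once training is over; the control group can begin directly after randomisation. The intervention group may also need more effort to apply the recommendations (Recruitment). If finishing differs between arms, a comparison among finishers no longer has the protection of randomisation. Involving the target group is one of the guideline's 21 recommendations, and piloting is a goal of module 2, so readers will look at this outcome to see whether the training worked. With 13 providers per arm, a few missing values can move the percentages a good deal.

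**Working it through.** The plan gives no power, event rate or completion rate for DEVELOPMENT, so there is no figure of its own to reproduce. Its sample-size statement (26 provider groups, 13 per arm, 1.5 SD, 90% power) concerns the primary t test. It reproduces (91.7% with 11 per arm, by the noncentral t distribution) and is not touched by this point.

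**Reading the sections together**

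1. Can MAPPinfo provide the value? No. The instrument rates only what is visible in the item and leaves out development methods.
2. Is there another source? The self-declaration is the plausible one, since its stated purpose includes mapping the development process. No sentence links it to DEVELOPMENT.
3. Who is asked? Procedure limits the t3 request to completers. Process evaluation speaks of all providers in both arms, but after completion. The expert interviews follow the self-declaration, so they reach the same providers.
4. Are non-finishers foreseen? Yes, by the extension and the rule on unfinished material.
5. Does another rule fill the gap? Not as worded. Coding as zero applies to criteria failing the MAPPinfo requirements, in the context of rating the primary outcome. Treating incomplete information as non-missing stands in the text on imputing the primary outcome.

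**What the denominator can do (assumed counts, none from the document)**

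Suppose 6 of 13 providers in each arm truly involved their target group, so the true difference is 6/13 − 6/13 = 0. All control providers finish. Observed proportion = involved finishers ÷ finishers.

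| Intervention non-finishers | Intervention observed | Control observed | Difference (points) |
|---|---|---|---|
| none | 6/13 = 46.2% | 6/13 = 46.2% | 0 |
| 2, neither involved | 6/11 = 54.5% | 46.2% | +8.4 |
| 2, both involved | 4/11 = 36.4% | 46.2% | −9.8 |
| 4, none involved | 6/9 = 66.7% | 46.2% | +20.5 |
| 4, all involved | 2/9 = 22.2% | 46.2% | −23.9 |

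The sign depends on what the non-finishers did, which is the information not collected. If all 13 per arm were asked and answered, every row would return 0.

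The nominal test result can change too. With assumed counts of 8/10 v 4/12 among finishers (80% v 33%), Fisher p = 0.043. With all randomised providers in the denominator and non-finishers counted as not fulfilled, 8/13 v 4/13 (62% v 31%) gives p = 0.24.

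**The case against.** The sections can largely be reconciled. DEVELOPMENT carries a label outside the four MAPPinfo categories, the article says such criteria need other sources, and it describes one. On that view only a cross-reference is missing. This stands against any claim that the outcome cannot be measured at all. It does not answer who is asked.

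A reader might infer that the form has no question on target-group involvement, because the topics named are options and outcomes, searches, extraction and appraisal, and "reasons for the use of pictures, graphics, fact boxes, value clarification tools, animations and interactive tools". The document does not support that. It is a one-sentence summary, in a journal article, of a form that is not shown; the question may well be there.

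No sentence sets a finishers-only denominator, and handling of missing secondary values is commonly left to the analysis plan. That is fair. But an analysis rule can only assign a value to providers who were never asked; it cannot recover what they did. The collection rule is stated, and it creates the gap.

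The training takes five days against 10 months plus a possible 2, so completion may hardly differ by arm. That may prove so, and it limits how large the problem is likely to be.

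**Conclusion.** The point holds in a limited form. A stated collection rule leaves DEVELOPMENT unobserved for providers who do not finish, whom the article itself expects, and the between-arm comparison would then be conditioned on a post-randomisation event. Size and direction of any bias cannot be computed from the document. If all providers finish, there is none. One of five secondary outcomes is affected, in a trial whose Discussion already concedes that its small sample limits secondary analyses.

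Three stronger readings go too far:

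- That the intervention does affect completion. The later start and possible extra effort make this plausible; no completion figures are given.
- That the plan builds in a bias of a given size. For example, 4/10 v 4/13 (40% v 31%) looks like a 9-point benefit when the count is 4 of 13 in each arm. It assumes three intervention non-finishers, none of them involvers, and no control non-finishers; Fisher p is about 0.69 even then.
- That an intention-to-treat promise is broken. That promise covers the primary analyses only.

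**What to change.** 1. In Secondary outcomes, state that DEVELOPMENT is rated from the self-declaration, not from MAPPinfo.
2. In Procedure and Process evaluation, request the self-declaration at t2 from every randomised provider, whether or not the item is finished, and make sure it covers target-group involvement and the method used.
3. In the analysis section, compare all randomised providers, with those giving no information counted as not fulfilled. This follows the zero-coding already used for unmet MAPPinfo criteria. Add a sensitivity analysis on available data.

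The cost is one earlier form request and a few sentences. The scoring rule has a price: a provider that involved its target group but returns no declaration counts as a failure. In the last row of the table, four such intervention providers would give 2/13 = 15.4% v 46.2%, a difference of −30.8 points against −23.9 on available data. Asking everyone at t2 should keep such cases few, and the sensitivity analysis shows how far the result depends on them.

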#### Sample size

The sample size was calculated for a t test comparing the IG and the CG regarding guideline compliance to EBHI as measured by MAPPinfo. It is assumed that MAPPinfo is normally distributed with the same standard deviation (*σ*) of 10% in both groups. Pretest data from MAPPinfo showed very low ratings for online-available health information. The quality of this information could be improved with just a little effort. Based on these assumptions and a sample size of 26 provider groups (13 in each study group), a quality improvement of 1.5* *σ* corresponding to a very strong Cohen’s effect size can be detected with 90% power using a two-sided significance level of 5% after excluding at the most 10% dropouts. The power was calculated using the statistical software package SAS version 9.4 (PROC POWER).

#### Procedure

During recruitment, both groups will be informed about the requirement to produce a health information item within 10 months, according to the defined criteria.

In a personal meeting, information on the requirements for study participation will be given and the providers must agree to comply with these requirements. The topic chosen for preparing the work sample will be defined. Written informed consent will be obtained from the individual participants. Consent will be obtained for the assessment of baseline data, for performing a critical health literacy test and for interviews within the process evaluation. Afterwards, baseline data will be assessed (*t*_− 1_) and randomisation will be performed (*t*_0_) (see the SPIRIT Figure, Fig. 3). In the IG, the workshop for the persons responsible (module 0) will be conducted and a timely convenient appointment for the training programme (modules 1 and 2) will be made (*t*_1_). The training should take place on-site at the provider’s institution. If possible in terms of time and place, two or more groups could attend the training together. When the training is completed, they can begin with their production of the work sample. The providers in the CG can start directly after the randomisation. During the time of production, we will contact the providers every 2 months to keep ourselves informed about the progress and to ask about any unexpected difficulties. The study team will be accessible and will answer upcoming questions regarding requirements and the course of the study. The IG will have access to the training material on the online learning platform, including resources such as updated search strategies. We realise that the lack of access to relevant references is an important barrier in the development process and, therefore, the providers in the IG and CG will equally receive support regarding the acquisition of research articles. No further support will be provided.

**Fig. 3 Fig3:**
[figure not shown]
Standard Protocol Items: Recommendations for Interventional Trials (SPIRIT) Figure

Completed health information can be sent to the study team at any time. After 10 months, the development process should be concluded and the providers will be asked for the material. A provider who cannot deliver after 10 months can be given a 2-month extension of the deadline. The provider should give a justification for the delay and a reasonable timeline for the following 2 months.

After 12 months (*t*_2_), even unfinished material must be submitted. The information will be rated with regard to the primary outcome. Single criteria (or else the entire information) that do not meet the MAPPinfo requirements, are coded as zero. Providers of both groups (IG and CG) who completed their information will be asked to give further information on the development process (*t*_3_). Interviews will be conducted in the IG to explore barriers and facilitators of implementation (cf. process evaluation). The providers in the CG will be invited to make appointments for the training programme (*t*_3_). After the provided information has been rated, providers may receive individual feedback on their material. This is optional, but this way the feedback would benefit especially the providers in the CG.

#### Data management, protection and analyses

Data survey and data processing are used for the scientific purpose of the study only and are appropriate and indispensable for that purpose. Figure 4 shows the data flow. Risk assessment according to §35 General Data Protection Regulation (DS-GVO) revealed a very low risk for the planned study. Special categories containing personal data will not be collected. In addition, the assessment using the Black List/White List of the competent supervisory authority of Saxony-Anhalt did not reveal the necessity for a privacy impact assessment. The remaining very low risk can be further minimised by the planned procedures (e.g. data storage using password-protected servers at the computer centre, no disclosure of data to third parties).

**Fig. 4 Fig4:**
[figure not shown]
Data flow

Withdrawal from the study is possible at any time without giving reasons and without disadvantages for the participants. In the case of withdrawal, data can be deleted only before anonymisation (after completion of the analysis). Privacy and data protection will be taken into account according to the German Data Protection Act [37]. A unique code number will be assigned to every participant. All data will be marked with this code number and, thus, pseudonymised. Identification of single participants is only possible with the coding key, which is stored on password-protected servers at the Martin Luther University Halle-Wittenberg. Only the project team has access to the coding key which is protected securely from third parties. Once data analysis has finished, the coding key will be deleted. From then on, data can no longer be deleted in the case of withdrawal from the study.

All data provided by the study participants are treated as absolutely confidential. Researchers adhere to the data protection rules. All data will be stored on password-protected servers and there will be no disclosure to third parties. Publication and storage of data will only be performed in an anonymised form. Audio-recordings will be deleted after transcription. Data will be stored at the Martin Luther University Halle-Wittenberg for 10 years.

The primary analyses will be performed from the intention-to-treat (ITT) perspective. The provider’s characteristics (institutional and individual level) will be analysed descriptively. Baseline variables of individuals will be described on the individual level by means, standard deviations, percentiles and frequency tables, depending on their distributions. The IG and CG will be described separately.

The primary outcome will be analysed on the provider level assuming approximately normal distribution by comparing means between the IG and CG using the *t* est. The distribution of MAPPinfo will be described graphically. In case of deviations from the normal distributions, transformations or alternative tests will be discussed as secondary sensitivity analyses. Frequencies of missing values will be described in detail. Multiple imputations will be performed for the primary outcome if there is enough information available. Only a few missing values are expected because the coding by the raters is very dependable. Incomplete health information will be considered and analysed as non-missing. The imputations will be performed if three values or fewer (12%) of the primary outcome (the outcome score, not the single items) are missing. The multiple imputation model will be fitted using the baseline variables of providers. For the binary secondary outcomes, relative frequencies will be described in both provider groups and compared using Fisher’s exact test. A secondary per-protocol analysis will be performed as a complete case analysis (without multiple imputations for the primary outcome). The secondary per-protocol analysis is planned to compare the results between ITT and per-protocol and to discuss a possible bias from protocol violations and missing values.

A data monitoring committee will not be necessary as the trial does not involve a high-risk intervention and participants do not belong to a vulnerable population. We do not expect adverse events or other unintended effects of the intervention. During the entire study period, participants will be able to contact the study centre, if necessary.

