### Eligibility and recruitment

#### Eligibility criteria

Providers will be eligible if they are responsible for the production and publishing of health information. The use of external services (e.g. counselling by experts, graphic design, external performing of pilot tests or external literature searches) is not a reason for exclusion, as long as the provider is designated as the responsible publisher/editor. Providers should have published information both regularly and currently. Therefore, they are eligible if they have published any information in the last 18 months. In addition, at least a single health information item produced in the last 3 years has to fulfil the following criteria: The information:
has to inform a health-related decisionhas to address patients or medical laypersonshas to discuss different options regarding one specified health problemdoes not inform about a single option, procedure or healthcare system andit does not give general advice on health and wellbeing

It is essential that the participating providers agree to comply with the training programme and the production of one item of health information. Above all, the providers will be notified about the purpose and schedule of the intervention and their obligation to produce the new health information within 10 months.

Members of the working groups on the *guideline evidence-based health information* or the GPGI are not eligible. The same applies to providers producing exclusively (drug)-fact(s) boxes or offering counselling services such as medical online consulting websites, health related blogs, forums or communities or (online) encyclopaedias.

Individuals in the institution or working group who are closely involved in the development of the health information will be included in the study and, if possible, all of them should attend the training. Staff turnover or other changes during the study period will be documented. New staff members will also have the opportunity to attend the training. The providers themselves will choose the participants according to their working processes and resources. No further eligibility criteria will be defined.

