### Randomisation and blinding

The concealed allocation of participating provider groups to either the intervention or the control group (CG) will be determined by randomisation, using a computer-generated list with randomly permuted blocks of length 2, 4, 6 or 8. An independent external person will prepare sealed, opaque envelopes. After the baseline assessment of the respective provider group, the researchers will open the sealed, opaque envelope and reveal the centre’s allocation on-site.

Due to the nature of the intervention, blinding of the participating providers and the researchers conducting the training programme is not possible. However, the assessment of the primary endpoint and all analyses will be blinded towards group allocation.

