## Discussion

The aim of the proposed trial is to evaluate the efficacy of the *guideline evidence-based health information* in combination with a training programme for providers of health information in comparison to having access to the guideline on its own. We expect the combined intervention to improve the quality of health information and thus promote informed patient decisions.

However, the training programme is extensive and time consuming; it does not only provide guidance on the application of the guideline but also extensive ebm knowledge. That is because a previous qualitative study revealed the providers’ shortcomings regarding their ebm competences. Participants must be released from their work duties in order to attend the training and, in addition, the development of information in compliance with the guideline recommendations is time and cost-intensive, e.g. comprehensive literature searches must be conducted by the providers themselves or contracted out. The lack of access to databases or references can constitute a further barrier. These potential barriers may limit the study results because of problems in recruitment and study compliance (attending the training programme in person and online; producing information in accordance with the requirements). To address the barriers, the providers will receive comprehensive information on the study course and its requirements, incentives will be provided (publicity for providers of high quality information) and the providers will receive support for purchasing literature. The attitudes of the providers regarding EBHI will play a crucial role and, therefore, these attitudes will be addressed in the training programme and additionally in the workshop for the providers in charge of health information publications. The freedom of choice regarding the topic of the information to be delivered as a working sample might lead to increased internal variance and, therefore, make it more difficult to detect an intervention effect. On the other hand, this method will safeguard both the motivation of the participant to cooperate and the ecological validity. As experience shows the variability on the quality spectrum to be also quite low between topics, we are nevertheless optimistic of being able to demonstrate an effect, even if the small sample size of providers can detect only strong effects of the intervention and limits detailed secondary analyses.

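### The primary analysis is an unadjusted t test although the same score is measured at baseline: a valid choice, but a cheap gain in precision is left unused

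*Protocol article*

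**What the plan says.** All references are to the protocol article.

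- **Primary analysis** (Data management, protection and analyses): "The primary outcome will be analysed on the provider level assuming approximately normal distribution by comparing means between the IG and CG", using a t test. No covariate is named. The section Sample size sizes the trial for the same test.
- **Baseline score** (Quality of health information, under Baseline variables): MAPPinfo, which also measures the primary outcome, is applied to one existing item per provider, namely its "most recent health information, which meets the criteria of materials giving information towards a health-related decision, will be rated regarding quality".
- **Availability** (Eligibility criteria): "at least a single health information item produced in the last 3 years has to fulfil the following criteria". A baseline item should therefore exist for every provider. The section Procedure places the baseline assessment before randomisation.
- **Other use of baseline data** (Data management, protection and analyses): apart from description, the one stated use is imputation: "The multiple imputation model will be fitted using the baseline variables of providers".
- **Randomisation** (Randomisation and blinding): allocation is made "using a computer-generated list with randomly permuted blocks of length 2, 4, 6 or 8". No stratification factor is mentioned.

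**The concern.** A pre-randomisation measurement of the outcome is often the best single predictor of the follow-up value. If it predicts follow-up at all well, putting it in the model removes explained variance from the treatment comparison and narrows the confidence interval at no cost in data. The trial has 26 providers, and its own Discussion accepts that only strong effects can be detected. What is at stake is precision, mainly if the true effect is smaller than the 1.5 SD used for planning.

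The timing of the decision also matters. In a trial this small a visible baseline difference between arms is quite possible, and an adjustment added after seeing it would look data-driven. Deciding beforehand avoids that.

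**Working it through.** **Inputs from the section Sample size.** 13 providers per arm; a standard deviation "of 10% in both groups"; target difference 1.5 SD, that is 15 percentage points; two-sided 5% level; 90% power; at most 10% dropout.

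**Assumed input.** The correlation rho between baseline and follow-up MAPPinfo within arm is not given. The range 0 to 0.7 is used.

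**Step 1: the plan's own figure.** The exact power of the two-sample t test comes from the noncentral t distribution with noncentrality d / √(1/n1 + 1/n2) and n1 + n2 − 2 degrees of freedom. At d = 1.5:

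- 10 per arm gives 88.7% and 11 per arm gives 91.7%, so 11 per arm are needed.
- 11 / 0.9 = 12.2, rounded up to 13 per arm, or 26 in total. The stated sample size reproduces.
- Power is 95.6% with all 26. With 23 analysed (12 v 11, about 10% dropout), √(1/12 + 1/11) = 0.4174, noncentrality is 1.5 / 0.4174 = 3.59 on 21 df, and power is 92.9%.

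**Step 2: the same trial with baseline adjustment.** For ANCOVA with one covariate, N = n1 + n2:

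noncentrality = d / √[(1 − rho²) × (1 + 1/(N − 4)) × (1/n1 + 1/n2)], with N − 3 degrees of freedom.

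The factor 1 + 1/(N − 4) is the average price of chance covariate imbalance. For N = 23 it is 1 + 1/19 = 1.053. At rho = 0.5 the standard error in SD units is 0.4174 × √(0.75 × 1.053) = 0.371, so the noncentrality at 1.5 SD is 1.5 / 0.371 = 4.04 on 20 df.

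| 12 v 11 analysed | Power at 1.5 SD | Power at 1.0 SD | Difference detectable with 90% power |
|---|---|---|---|
| t test | 92.9% | 62.7% | 1.42 SD |
| ANCOVA, rho 0 | 91.5% | 60.3% | 1.46 SD |
| ANCOVA, rho 0.3 | 93.7% | 64.4% | 1.39 SD |
| ANCOVA, rho 0.5 | 97.0% | 72.7% | 1.26 SD |
| ANCOVA, rho 0.7 | 99.7% | 87.5% | 1.04 SD |

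Simulation with 20,000 runs per setting gave 91.4%, 93.5%, 96.8% and 99.6% for the four ANCOVA rows at 1.5 SD, in agreement.

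**Step 3: break-even.** At 1.5 SD the two analyses have equal power at rho = 0.22 (13 v 13) and rho = 0.23 (12 v 11). Below that, ANCOVA is slightly worse.

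**Step 4: worst case.** At rho 0 and 1.5 SD, power falls from 95.6% to 94.7% with 26 providers and from 92.9% to 91.5% with 23. Both stay above 90%. At 1.0 SD with 23 the loss is 62.7 − 60.3 = 2.4 points.

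**The case against.** **The t test is correct as planned.** It is valid and unbiased over randomisation, it matches the sample size calculation, and it meets the stated power. This stands in full. A reader might infer that the primary analysis is wrong or the trial underpowered for its target; the document does not support either.

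**Rho is unknown and may be weak.** The baseline item is a different product: it may be up to 3 years old and on another topic, and the number of checklist items varies with the type of decision. Pretest ratings were very low, so a floor effect is possible. Follow-up scores also include zeros for unmet criteria and unfinished material, which need not track earlier quality. Against this, the Discussion reports little variation in quality between topics, so a change of topic alone need not destroy the correlation. The objection stands as far as the gain cannot be promised.

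**Chance imbalance is not a second defect.** With 13 per arm, the baseline mean difference has a standard error of √(2/13) = 0.39 SD, so a difference above 0.5 SD arises in about 20% of randomisations. A reader might take this as bias in the unadjusted estimate. It is not: that variation is already in the t test's standard error. It is the same lost precision, viewed conditionally on the observed baseline.

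**The Discussion's remark on variance does not help the case.** Free choice of topic "might lead to increased internal variance and, therefore, make it more difficult to detect an intervention effect". A reader might see baseline adjustment as the remedy. A score on an item about a different topic cannot remove variance due to the follow-up topic; if that variance is large, rho is lower.

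**An adjusted sensitivity analysis may stand in a statistical analysis plan not shown.** Its absence from the article is therefore not held against the plan. The point concerns the primary test, which the article does fix.

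**Conclusion.** The point holds as a low-severity suggestion on efficiency. The primary comparison sets aside a pre-randomisation score on its own outcome instrument, which should be available for every provider.

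With 23 analysed, adjustment changes power at the planned 1.5 SD by −1.4 points (rho 0), +0.8 (rho 0.3) or +4.1 (rho 0.5). At a true effect of 1.0 SD the changes are −2.4, +1.7 and +10.0 points. The benefit is thus small at the planning effect and becomes material only if the true effect is smaller and rho is about 0.5 or more.

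These figures rest on the protocol's SD of 10 points, approximate normality, a common linear slope in both arms, and a rho that is assumed. Larger gains can be shown by taking a 10-point effect, no dropout and rho of 0.7, but nothing in the document singles out those values. The case for the change is its asymmetry: a small, bounded loss against a possibly useful gain, using data already collected.

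**What to change.** In Data management, protection and analyses, prespecify as primary a linear model of the follow-up MAPPinfo score on randomised group and baseline MAPPinfo score, with that single covariate. Report the adjusted mean difference with its 95% confidence interval. Keep the unadjusted t test as a sensitivity analysis. Any statistical analysis plan should carry the same wording, settled before outcome data are seen.

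The cost is a sentence or two of text and one degree of freedom. If the baseline score proves unrelated to the outcome, the price is the 1 to 2 points of power shown above. No new data and no change in sample size are needed.
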